### Ethics and consent

The present trial protocol is performed in accordance with the Declaration of Helsinki (version October 2008; 49th General Assembly of the World Medical Association, Somerset West, Republic of South Africa) and approved by the institutional review board from the Research Ethics Committee of the Chamber of Physicians Westfalen-Lippe and the Westfalian Wilhelms University of Münster.

Data collection will be performed pseudonymously and the patient’s name will not appear on any case report form (CRF) or in any other trial document. All data will be kept confidential. Consent procedures follow local requirements, as approved by the ethics committee of the University of Münster. The treating investigator will inform the patient about the nature of the trial, its aims, expected advantages as well as possible risks. Written informed consent will be obtained from eligible patients and in case of patient incapacity by the legally authorized representative (see Additional file 2). In case of an emergency situation a consultant physician who is independent of the investigational team will be involved. Once the participant regains capacity or the legally authorized representative is available, he/she will be asked to affirm or withdraw consent.

### Objectives and aims

#### Aim 1

To compare the clinical efficacy between early and late initiation of renal replacement therapy in critically ill patients with AKI, we are testing the following:Hypothesis I: early initiation of renal replacement therapy in the treatment of critically ill patients with AKI will reduce mortality at 90 days compared to late initiation.

#### Aim 2

To understand the mechanisms of illness and recovery and how the RRT implementation strategies affect them, we are testing the following:Hypothesis II: early and late RRT are associated with differences in the expression of markers of illness and recovery.

#### Aim 3

We aim to assess the costs and cost-effectiveness of both strategies.

### Statistical analysis

Statistical analyses will be performed according to the principles of the ICH guideline E9 ‘Statistical principles for clinical trials’ [19] using standard statistical software (IBM SPSS Statistics, Armonk, NY, USA).

### Power and sample size

Power calculations are performed based on the primary endpoint, i.e. the overall survival in a 90-day follow-up period. The primary efficacy analysis is intended to test whether early versus late initiation of RRT in intensive care patients with AKI results in different overall survival in a 90-day follow-up period.

An adaptive design based on a group sequential plan according to O’Brien and Fleming with one interim analysis and a global (two-sided) significance level α = 0.05 is applied (see below). The expected 90-day mortality rate in the control group with late initiation of RRT is 55 % (based on literature research [7–10, 20–24]). Differences between treatment groups are to be detected with a power of 80 %, if the 90-day mortality rate in the experimental intervention group with early initiation of RRT is 37 % or smaller. The expected treatment effect of 18 % is calculated on the mortality differences between the early and late groups resulting from the studies of our literature research [7–10, 20–24] (see Additional file 3). The interim analysis is conducted at the time when half of the total number of deaths has been observed (information rate 0.5). Follow-up of each patient will be 90 days. Resulting from these considerations, the interim analysis is performed after 53 deaths have been observed across both treatment groups. The final analysis is planned to be performed after 106 deaths have been observed in total across both treatment groups, i.e. assuming an average of 46 % mortality rate in the 90-day follow-up period, a total number of 106/0.46 = 230 patients across both treatment groups is included in the final analysis. This corresponds to 256 recruited patients, if an expected number of 10 % of recruited patients is assumed to be lost to follow-up and in the worst case has completely non-evaluable data. Power calculations are to be performed based on a two-sided inverse normal log-rank test [25], using ADDPLAN software (ICON, Dublin, Ireland).

### Interim analysis

A group sequential plan according to O’Brien and Fleming with one interim analysis is established. In order to maintain a global significance level alpha = 0.05, the interim and the final analysis are performed on local significance levels of 0.0052 and 0.0480, respectively. Based on the group sequential plan, an adaptive design is applied, that admits two possible design changes after the interim analysis: i) the number of deaths of the final analysis will be re-calculated applying the inverse normal method [26]; and ii) the schedule and the number of further interim analyses may be modified applying the conditional rejection error probability (CREP) principle [27, 28].

#### i) Re-calculation of the number of deaths of the final analysis applying the inverse normal method

The basic idea of the inverse normal method is to transform the *p* values of successive stages of a multistage trial to normally distributed test statistics that can be processed using group sequential methods. In particular, let *p*1 and *p*2 denote the *p* values of the interim and final statistical analysis, respectively. Then in the final analysis the null hypothesis is rejected if:$$ C\left(p1,p2\right):=1-\varnothing \left[\sqrt{\frac{1}{2}}\kern0.5em \cdotp \kern0.5em {\varnothing}^{-1}\left(1-p1\right)+\sqrt{\frac{1}{2}}\kern0.5em \cdotp \kern0.5em {\varnothing}^{-1}\left(1-p2\right)\right]\le {\alpha}_c. $$

The term *α*_*c*_ is determined so that the overall type I error is controlled.

Interim data on the primary outcome comprise the treatment arm, the date of randomization, a status indicator of death within 90 days post-randomization, as well as the data of death or last follow-up. Using these data the conditional power of a significant final result is calculated: a) based on the observed hazard ratio of early versus late initiation of RRT at the time of the interim analysis; as well as b) based on the originally assumed hazard ratio. The number of deaths of the final analysis is determined as follows:If the originally planned number of deaths of the final analysis yields a conditional power larger than (1 − *β*_*upper*_^*cond*^) calculated according to both approaches a) and b), then the originally planned number of deaths is kept unchanged.If in one or both of the two approaches a) and b) the conditional power is between (1 − *β*_*lower*_^*cond*^) and (1 − *β*_*upper*_^*cond*^), then the number of deaths of the final analysis is increased, so that in both approaches a) and b) the conditional power is at least equal to (1 − *β*_*upper*_^*cond*^). In any case, however, the maximum number of additionally recruited patients in the second stage of the trial is restricted to an upper limit of 350 patients.If in both approaches a) and b) the conditional power is lower than (1 − *β*_*lower*_^*cond*^), then no further patient is recruited and the study is stopped.

The values (1 − *β*_*lower*_^*cond*^) and (1 − *β*_*upper*_^*cond*^) are kept confidential in order to preserve the integrity of the trial. Otherwise, if the number of additionally recruited patients in the second stage of the trial is announced, this information could be used to disclose the results of the interim analysis.

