### Primary outcome analyses

The primary efficacy analysis will include all randomized patients (full analysis set) and will be performed according to the intention-to-treat principle, i.e. all patients are analyzed in the group to which they were randomized (Fig. 2). The effect of early initiation of RRT versus late initiation of RRT on overall survival in a 90-day follow-up period will be assessed by comparing the randomized groups with a (two-sided) inverse normal log-rank test [21]. If the difference in overall survival is significant, the treatment effect will be estimated by means of the 90-day all-cause mortality rate in both treatment groups. The primary intention-to-treat analysis of the primary outcome provides confirmatory statistical evidence.

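### The inverse normal rule takes p2 from the final analysis instead of the second-stage deaths, so followed as written the confirmatory test has a type I error of about 9 to 13%, not 5%

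*Protocol article*

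**What the plan says.** All references are to the protocol article.

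- **Interim analysis, subsection i)** introduces the inverse normal method as a way to transform p "values of successive stages of a multistage trial to normally distributed test statistics". It then defines p1 and p2 as the p "values of the interim and final statistical analysis, respectively". The null hypothesis is rejected at the end if 1 − Φ[√½·Φ⁻¹(1−p1) + √½·Φ⁻¹(1−p2)] ≤ αc. No number is given for αc; it is said to be chosen so that the overall type I error is controlled. The sidedness of p1 and p2 is not stated. The same subsection lets the final number of deaths depend on the interim data.
- **Power and sample size** fixes what the final analysis is: "The final analysis is planned to be performed after 106 deaths have been observed in total across both treatment groups". The interim is at 53 deaths. A "global (two-sided) significance level α = 0.05 is applied", with 80% power.
- **Interim analysis** gives the boundaries: "the interim and the final analysis are performed on local significance levels of 0.0052 and 0.0480, respectively".
- **Primary outcome analyses** describes the confirmatory test as "comparing the randomized groups with a (two-sided) inverse normal log-rank test".

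**The concern.** The combination rule is valid when the two p values come from separate data: p1 from the first 53 deaths, and p2 from what accrues afterwards. Only then is the weighted sum of the two normal scores standard normal under the null hypothesis, because ½ + ½ = 1. The definition of p2 points to the final analysis, which includes the first 53 deaths. Stage 1 is then counted twice, the two scores are positively correlated, and the sum has a variance above 1. Judged against a boundary made for variance 1, it rejects too often.

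This is the trial's only confirmatory test, and the sentence defines the inputs to its formula. An analyst who programs it as worded would report a result as significant at 5% from a test with a considerably larger false-positive rate.

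A second, smaller gap compounds this. The formula is directional (small p means evidence in one direction), while the test and its local levels are two-sided, and nothing says how the two are joined.

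**Working it through.** **Inputs (protocol article).** Global two-sided α 0.05; local levels 0.0052 and 0.0480; 53 interim and 106 final deaths; 90-day mortality 55% (late) and 37% (early); 80% power; 1:1 allocation; 10% loss to follow-up. Calculations for 106 deaths assume no change in the death count and no futility stop. Log-rank statistics are treated as normal with information d/4.

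**1. The plan's own figures reproduce under stage-wise, one-sided p values.**
- Hazard ratio = ln(0.63)/ln(0.45) = 0.579, |ln HR| = 0.547.
- The two-look O'Brien-Fleming constant at information 0.5 is 1.9774. Final level 2·(1−Φ(1.9774)) = 0.0480; interim level 2·(1−Φ(1.9774·√2)) = 0.0052.
- Total two-sided α at these levels, from the bivariate normal with correlation √0.5, is 0.0500.
- Drift at 106 deaths = √(106/4)·0.547 = 2.816. Power = 80.1%.
- 106/0.46 = 230; 230/0.9 = 256.

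**2. What the correct rule does.** Let Z_1 be the statistic at d1 = 53 deaths and Z_all the statistic at d deaths. The second-stage increment is Z2 = (√d·Z_all − √d1·Z_1)/√(d − d1). With d = 106 this is √2·Z_all − Z_1, so (Z_1 + Z2)/√2 = Z_all. Without adaptation the rule reduces to the ordinary log-rank statistic at 106 deaths, for which ±1.977 is the right boundary.

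**3. Literal p2, one-sided p values, 0.024 per direction.** The statistic becomes (Z_1 + Z_all)/√2.
- corr(Z_1, Z_all) = √(53/106) = 0.707.
- Variance = 1 + 0.707 = 1.707; SD = 1.307.
- Final-look error = 2·(1−Φ(1.977/1.307)) = 2·(1−Φ(1.513)) = 0.130. Adding the interim look leaves 13.0%. Power is 86%.
- At 151 total deaths, the count used as an illustration under the CREP principle: correlation √(53/151) = 0.592, SD = √1.592 = 1.262, error = 2·(1−Φ(1.977/1.262)) = 2·(1−Φ(1.567)) = 11.7%.

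**4. Literal p2, two-sided p values, αc = 0.048.** By simulation (4 million trials): type I error 9.0%, power 81%.

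**5. Could αc be recalibrated instead?** For 106 deaths the boundary would have to rise to 2.562 (2.562/1.307 = 1.96), a two-sided level of about 0.0104, with power about 74%. For 151 deaths it would be 1.262 × 1.962 = 2.476, a level of about 0.0133. The required value moves with the second-stage size, which may itself depend on interim data, so no single αc gives 5% across the permitted designs. Neither value agrees with the stated 0.0480.

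**6. Sidedness alone, with correct stage-wise p values.** If p1 and p2 were two-sided and αc = 0.048, simulation gives a type I error of 4.96% but power of 72%. About 45% of null rejections would then combine stages that point in opposite directions. Example: p1 = 0.20 favouring early and p2 = 0.02 favouring late give (0.842 + 2.054)/√2 = 2.047, C = 0.020, a rejection. The directional result is (1.282 − 2.326)/√2 = −0.74, two-sided p = 0.46.

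**The case against.** The context points to the correct method. The sentence before the definition names stage p values as the principle, the definition is offered as an instance of it, and the subsection later speaks of a second stage. The test is named as an inverse normal log-rank test with references, and every design figure reproduces under that reading. The article also says αc is set to control the type I error, and it is a condensed text whose analysis plan is not shown.

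Much of this stands. The intent is evident, and the calculation behind the design was evidently done correctly. An explicit increment formula or a printed αc could properly sit in an analysis plan. What does not stand is that the wording is harmless. This is not a missing detail but a stated definition that contradicts its own principle. The clause on αc does not rescue it: the Interim analysis section already fixes the final level at 0.0480, which fits only independent stages, and recalibration fails under adaptation (step 5).

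A reader might infer more than the document supports:
- **That p1 and p2 are defined as two-sided.** They are not. Only the test is called two-sided, and that can be run as two one-sided combination tests. The 72% power applies only if an analyst chose two-sided p values.
- **That the stated 5% and 80% both fail.** At the stated levels, no reading examined here breaks both. A cumulative p2 inflates the error while power is 81 to 86%; two-sided stage-wise p values keep the error near 5% and lose power.
- **That the error doubles because one-sided p values are set against 0.0480.** The protocol never makes that pairing; 0.0480 is a two-sided level, or 0.0240 per direction.

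**Conclusion.** The definition of p2 is wrong as written and should be corrected. Followed literally with the stated levels, the confirmatory test has a type I error of about 13% with one-sided p values (11.7% at 151 total deaths) or about 9% with two-sided p values, against a stated 5%. These figures are conditional on the literal reading, on the boundaries 0.0052/0.0480, and on the normal approximation to the log-rank test.

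The open sidedness is a lesser point to settle in the same sentence. The sample size, number of deaths, local levels and power are not in question. The defect lies in the wording of the test and not in the design.

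**What to change.** In subsection i) of the Interim analysis section:
- Define p1 as the one-sided log-rank p value from the first-stage data (the first 53 deaths).
- Define p2 as the one-sided p value of the second-stage increment only, Z2 = (√d·Z_all − √d1·Z_1)/√(d − d1), where d is the total number of deaths at the final analysis and d1 = 53.
- State that the combination test is applied in each direction, at 0.0026 for the interim and αc = 0.0240 for the final analysis, so that it matches the two-sided levels 0.0052 and 0.0480.

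Carry the same wording into the analysis plan and check that the analysis program uses the increment. With these definitions the overall two-sided error is 5.0% and power is 80.1% at 106 deaths. The cost is a few words of text; no patients, data or design figures change.

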#### ii) Modification of the schedule and the number of further interim analyses applying the CREP principle

Upon inspection of interim results beyond the re-calculation of the number of deaths, further possible design changes will be performed, i.e. a modification of the schedule and the number of further interim analyses. These changes will be done according to the CREP method [27, 28]. The CREP principle is a general method used in adaptive clinical trials. In an interim analysis based on current data, the CREP is calculated, that is the conditional probability that in the final analysis a significant result will be reached, under the initial study design, and under the null hypothesis, conditional on the information that is available so far. Denote this probability CREP_0_. The CREP principle then suggests that after the interim analysis a completely different design may be chosen – if the new design is constructed so that it provides the same conditional rejection error probability CREP_0_ as the initial design.

Modifications to the protocol will be made only in the form of written amendments and with the agreement of the study committee. The respective ethics committees will be informed of the modifications and patient information will be changed according to the modifications of the protocol.

Suppose, for example, that upon the inspection of interim results according to i) it is decided to continue to follow-up patients and to perform the final analysis at the time when 151 deaths have been observed in total across both treatment groups. Moreover, suppose that the calculated conditional rejection error probability at the time of the interim analysis amounts CREP_0_ = 0.04. In this case it may be decided to introduce another interim analysis before the final analysis is performed. Therefore, a new group sequential plan is established and implemented at the time of the (first) interim analysis. The new group sequential plan consists of one (further) interim analysis before the final analysis is performed after 151 deaths have been observed, and maintains a (two-sided) significance level alpha = CREP_0_ = 0.04. Concretely, the new group sequential plan may be established according to Pocock, so that the second interim analysis is performed after 53 + 49 = 102 deaths have been observed in total, and both the second interim and the final analysis are performed on local significance levels of 0.0233, respectively.

### Primary outcome analyses

The primary efficacy analysis will include all randomized patients (full analysis set) and will be performed according to the intention-to-treat principle, i.e. all patients are analyzed in the group to which they were randomized (Fig. 2). The effect of early initiation of RRT versus late initiation of RRT on overall survival in a 90-day follow-up period will be assessed by comparing the randomized groups with a (two-sided) inverse normal log-rank test [21]. If the difference in overall survival is significant, the treatment effect will be estimated by means of the 90-day all-cause mortality rate in both treatment groups. The primary intention-to-treat analysis of the primary outcome provides confirmatory statistical evidence.

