### Enrolment

Enrolment began in August 2013. Prior to being randomized into the study, the trial coordinators obtain consent for participation in the study (see Ethics and consent). Assuming all inclusion criteria are fulfilled and no exclusion criteria are met, each patient receives a study identification number and treatment allocation at enrolment. Patients are randomized in a 1:1 ratio to one of the two treatment arms using a computerized system. Randomization is stratified by SOFA Cardiovascular organ Failure Score (0–2 vs. 3–4) and by the presence or absence of oliguria. The randomization day is day 0.

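### Randomisation is stratified by cardiovascular SOFA and oliguria, but the primary log-rank test is stated without these strata; stratifying it would gain up to a few points of power if the factors are prognostic

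*Protocol article*

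**What the plan says.** The Enrolment section fixes the allocation scheme: "Randomization is stratified by SOFA Cardiovascular organ Failure Score (0–2 vs. 3–4) and by the presence or absence of oliguria". This gives four strata with 1:1 allocation.

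The Primary outcome analyses section defines the confirmatory test on all randomised patients as "comparing the randomized groups with a (two-sided) inverse normal log-rank test [21"]. The Power and sample size section rests on the same test: "Power calculations are to be performed based on a two-sided inverse normal log-rank test [25"]. The per-protocol sensitivity analysis names it once more. None of these places mentions the stratification factors.

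The Interim analysis section, under the re-calculation of the number of deaths, lists the interim data on the primary outcome: treatment arm, randomisation date, 90-day death indicator, and date of death or last follow-up. Conditional power is to be computed from these data. Neither stratification factor is on the list.

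Baseline risk enters only the further, non-primary Cox models. Their example covariates include the SOFA score but not oliguria.

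**The concern.** Stratified randomisation removes chance imbalance between the arms in the stratification factors. If those factors predict death, the log-rank numerator varies less from trial to trial than under simple randomisation. The ordinary log-rank variance does not know this. The standardised statistic is then too small on average, the true type I error falls below nominal, and some of the information secured by the randomisation is not used. Pooling patients with different hazards into one risk set also dilutes the treatment contrast.

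At stake is efficiency in the one confirmatory test. There is also a matter of pre-specification. The first-stage p value is carried into the final combination, and the interim result drives both the re-calculated number of deaths and the stopping decision. The form of the test therefore has to be settled before the first look.

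**Working it through.** **1. Reproducing the plan's own figures.** Inputs from Power and sample size and Interim analysis: "a global (two-sided) significance level α = 0.05 is applied"; "Differences between treatment groups are to be detected with a power of 80" %; 90-day mortality 55% (late) and 37% (early); one interim look at half of the deaths; "interim and the final analysis are performed on local significance levels of 0.0052 and 0.0480".

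- Hazard ratio = ln(1 − 0.37) / ln(1 − 0.55) = ln 0.63 / ln 0.45 = 0.579.
- Deaths, fixed design = 4 × (1.960 + 0.842)² / (ln 0.579)² = 104.9.
- Two-look O'Brien–Fleming plan at information 0.5: final critical value 1.977, interim 1.977 × √2 = 2.796. The local levels are 0.0052 and 0.0480. Required deaths are 105.7, so 106, with power 80.1%.
- Patients: 106 / 0.46 = 230; 230 / 0.90 = 256.

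The design reproduces. No strata enter the calculation.

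**2. The two tests.** Both use Z = U / √V, with U = Σ(tᵢ − pᵢ) and V = Σ pᵢ(1 − pᵢ) over deaths. Here tᵢ is 1 if the death is in the early arm, and pᵢ is the early-arm share of the risk set. The unstratified test uses one risk set of all patients. The stratified test forms risk sets within each of the four strata and adds up U and V.

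**3. Single-look simulation.** 230 patients, exponential survival, censoring at 90 days, two-sided 0.05, 8,000 runs per cell. Marginal mortality is held at 55% vs. 37% for power. The article does not give block size (4 used), prevalence or prognostic hazard ratios, so these are assumed. Monte Carlo standard error of the type I error is about 0.24 points.

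| Prognostic HRs of the two factors | Type I error, unstratified | Type I error, stratified | Power, unstratified | Power, stratified | Gain (points) |
|---|---|---|---|---|---|
| 1 and 1 | 5.4% | 5.3% | 79.9% | 79.7% | −0.2 |
| 1.25 and 1.25 | 5.1% | 5.1% | 79.9% | 80.1% | 0.2 |
| 1.5 and 1.5 | 4.5% | 5.0% | 80.1% | 81.5% | 1.4 |
| 2 and 2, prevalence 80/20 | 4.3% | 4.9% | 81.5% | 83.0% | 1.5 |
| 2 and 2 | 3.6% | 4.7% | 81.7% | 85.3% | 3.6 |
| 3 and 3 | 2.5% | 5.4% | 84.1% | 91.4% | 7.3 |

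Prevalence is 50/50 unless stated. A separate run of 4,000 trials at hazard ratios 2.5 and 2 (critical value 1.977 for power, 1.96 for the null) gave power 81.6% → 86.4%, a gain of 4.8 points, and type I error 2.9% unstratified vs. 4.9% stratified.

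**4. The staged test itself.** The inverse normal test was run with an interim at 53 deaths, levels 0.0052 and 0.0480, 230 patients and 55% vs. 37%. The second stage uses the increment Z₂ = (U_final − U_interim) / √(V_final − V_interim), combined as √½·Z₁ + √½·Z₂.

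| Prognostic HRs | Power, unstratified | Power, stratified | Gain (points) |
|---|---|---|---|
| 1 and 1 | 80.5% | 80.4% | −0.1 |
| 1.5 and 1.5 | 79.6% | 80.8% | 1.2 |
| 2 and 2 | 82.0% | 85.3% | 3.3 |
| 2.5 and 2 | 82.8% | 86.8% | 4.0 |

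In the two stronger settings the type I error was 3.2–3.4% unstratified and 4.9–5.3% stratified. Staging leaves the picture unchanged.

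**The case against.** **Silence is not a decision.** A reader might infer that the plan has chosen to disregard the strata. The article nowhere says that the test is unstratified, and as a condensed report it could leave this to the full protocol or SAP. That stands as a caution. Against it, the article is detailed here (combination formula, conditional rejection error principle, worked example), and a stratified interim statistic cannot be computed from the interim data it lists. As written, the test is unstratified.

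**Prognostic strength is unknown.** A reader might take both factors to be strong predictors of death. The article gives no figure for either. Its Discussion ties vasopressor-requiring hypotension to dialysis-dependent kidney injury, not to death. This stands in full: at hazard ratios of 1.25 each there is nothing to gain.

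**The plan keeps its power.** A reader might infer that the trial falls short of 80%. With the planned marginal rates, the unstratified test has 79.6–84.1% power in the tables above, so the target is met within simulation error. Power drops clearly only if 0.579 is read as the within-stratum hazard ratio (76.5% at prognostic hazard ratios of 2 each, against 80.4% stratified). The protocol states its assumption as group mortality rates, so that reading has no support.

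**The choice is coherent.** An unstratified test matches the power calculation and the marginal 90-day mortality rates reported after it. This is true, but those rates can be reported after a stratified test as well.

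**Conclusion.** The point holds as an efficiency improvement of modest size. The randomisation uses two factors that the primary test, as stated, does not. If the factors are prognostic, the unstratified test is conservative, with a true type I error of about 3–4.5% in the settings from 1.5 each to 2.5 and 2. It then gives up about 1 point of power at hazard ratios of 1.5 each, 1.5–4 points at 2 each (depending on prevalence) and 4–5 points at 2.5 and 2. With no or weak prognosis it gives up nothing. Hazard ratios, prevalence and block size are all assumptions.

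It would be wrong to conclude that the confirmatory result is invalid. The type I error was not inflated beyond simulation error in any scenario, and the sample size reproduces as stated.

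**What to change.** State in the Primary outcome analyses and Interim analysis sections that the primary log-rank test, at interim and final, is stratified by the two randomisation factors, with stage-wise stratified increments entered in the inverse normal combination. Add the two factors to the interim dataset, and use the stratified hazard ratio for conditional power. Keep the unstratified test as a sensitivity analysis and the 90-day mortality rates as the reported effect. If the full protocol or SAP already fixes a stratified test, it is enough to say so in these sections.

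Cost: slightly more analysis work, including in the conditional-power step. No extra patients are needed, since the factors are already required for allocation. If the strata prove not to be prognostic, the power loss is about 0.1–0.2 points, within simulation error.

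### The primary ITT treatment effect is to be estimated if the log-rank test is significant, so a non-significant or futility-stopped trial has no planned estimate for its confirmatory comparison

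*Protocol article*

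**What the plan says.** The primary endpoint is overall survival over 90 days, analysed by intention to treat in all randomized patients. Under Primary outcome analyses, the effect of early versus late initiation "will be assessed by comparing the randomized groups with a (two-sided) inverse normal log-rank test". The next sentence there, repeated under Outcomes, sets the estimation rule, which applies to each arm: "If the difference in overall survival is significant, the treatment effect will be estimated by means of the 90-day all-cause mortality rate". Neither place says what is estimated if the test is not significant. Neither names a between-group contrast or a hazard ratio.

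The design around the rule is two-stage. A "global (two-sided) significance level α = 0.05 is applied", and "the interim and the final analysis are performed on local significance levels of 0.0052 and 0.0480, respectively", after 53 and 106 deaths. The subsection on re-calculating the number of deaths also lets the trial stop at the interim if conditional power is too low under both of its assumptions.

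Some other analyses do not depend on significance:
- under Primary outcome analyses, a per-protocol log-rank test, a chi-squared test of 90-day mortality in per-protocol complete cases, and Cox models with a baseline-risk-by-treatment interaction;
- under Secondary and tertiary outcome analyses, Kaplan-Meier plots for survival data and contingency tables for binary data.

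**The concern.** A significance test says whether the boundary was crossed. It does not say how large the effect may be or which effects are excluded. After a significant result the direction is already clear. After a non-significant one, readers need the estimate and its interval to tell a result that rules out a useful benefit from one that does not. The rule provides the planned estimate in the first case and not in the second.

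This is a positive instruction for the confirmatory endpoint, given twice, and not a detail left open. An analysis plan that follows it inherits the condition. A trial stopped for low conditional power falls under it too, with even fewer deaths and a wider interval.

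**Working it through.** **Inputs** (protocol article, Power and sample size; Interim analysis)
- "The expected 90-day mortality rate in the control group with late initiation of RRT is 55"%; the "90-day mortality rate in the experimental intervention group with early initiation of RRT is 37"% or smaller
- "Differences between treatment groups are to be detected with a power of 80"%
- deaths at interim and final: 53 and 106; local two-sided levels 0.0052 and 0.0480
- 230 evaluable and 256 recruited patients, 1:1 allocation

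**1. Reproduce the design.** Under proportional hazards, HR = ln(1 − 0.37)/ln(1 − 0.55) = ln 0.63/ln 0.45 = 0.579. The local levels correspond to critical values of 2.794 and 1.977. With the variance of the log HR taken as 4/deaths, and the two statistics bivariate normal with correlation √0.5, the overall two-sided error is 0.0500 and the power at 106 deaths is 0.801. Also 106/0.46 = 230 and 230/0.90 = 256. The plan's figures hold.

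**2. Observed HR needed for significance.**
- Final: exp(−1.977 × 2/√106) = exp(−0.384) = 0.681. Against 55% control mortality, the early arm is at 1 − 0.45^0.681 = 41.9%, a difference of 13.1 points.
- Interim: exp(−2.794 × 2/√53) = 0.464, a difference of 24.0 points.

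**3. A result just short of the boundary.** Take an observed HR of 0.70 at 106 deaths. The early arm is at 1 − 0.45^0.70 = 42.8%, a difference of 12.2 points.
- Test statistic: 0.357/0.194 = 1.84, below 1.977, so not significant.
- Approximate 95% interval: 0.70 × exp(±1.96 × 2/√106) = 0.70 ÷ 1.463 to 0.70 × 1.463 = 0.48 to 1.02.
- With 1.977 in place of 1.96: 0.48 to 1.03.

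The interval contains the design HR of 0.58. The trial would not have excluded the effect it was built to find, yet the rule triggers no estimate.

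**4. How often this arises.** The chance of a non-significant result is 1 − power. These figures use fixed 53/106 deaths and stopping at the interim only for significance; the last two columns come from 2,000,000 simulated trials per row.

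| True HR | True difference (points) | Non-significant | Mean HR in those trials | Mean difference in those trials (points) |
|---|---|---|---|---|
| 0.579 (design) | 18.0 | 19.9% | 0.76 | 9.5 |
| 0.70 | 12.2 | 55.3% | 0.80 | 7.5 |
| 0.80 | 7.8 | 79.2% | 0.86 | 5.3 |

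Only the first row is the protocol's own assumption. The other two are illustrations.

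**5. Precision.** With 115 patients per arm, the 95% half-width for the mortality difference is 1.96 × √(0.55 × 0.45/115 + 0.37 × 0.63/115) = 12.7 points. A non-significant result can therefore be compatible with a large benefit, and only an interval would show it.

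**The case against.** **The text says if, not only if, and other analyses are unconditional.** True, so a reader who infers that a null trial would report no effect information at all goes too far. But the substitutes are incomplete. The chi-squared test of 90-day mortality is per-protocol and complete-case. The Cox models are there to study risk interaction. The Kaplan-Meier plots and contingency tables are described for secondary endpoints. The abstract counts 90-day mortality among these, but the list under Outcomes has only 28-day, 60-day and 1-year survival. None is designated as the ITT estimate for the confirmatory comparison.

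**The condition does not inflate a positive result.** A reader might infer that it does. In the same simulation, significant trials average 21.0 points against a true 18.0 at the design effect. But that comes from selecting on significance and from early stopping. A significant trial reports the same number with or without the condition.

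**Lost patients are not dropped from the primary analysis.** The sample-size section says that 10% "of recruited patients is assumed to be lost to follow-up", and a reader might infer a crude rate in completers. If all the lost patients were survivors and were dropped, 37% and 55% would become 0.37/0.90 = 41.1% and 0.55/0.90 = 61.1%. The documents do not support this. The 10% is a sample-size allowance, the primary analysis includes all randomized patients, and complete-case restriction is stated only for the per-protocol analyses. A 90-day rate can equally be a Kaplan-Meier estimate.

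**Mortality by arm suits the hypothesis, and interval methods belong in an analysis plan.** Both points stand. The choice of 90-day mortality is not the fault, and the absence of interval methods is no finding. The fault is the stated condition.

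**Conclusion.** The point holds for the primary ITT estimate. As written, the plan provides for one after a significant log-rank test and for none after a non-significant result or a futility stop. At the protocol's assumed effect, about one trial in five would be non-significant, and the share rises if the true effect is smaller.

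The test, its error control and the sample size are unaffected, and nothing here shows bias in a reported estimate. The point deserves correction before analysis but does not threaten the validity of the confirmatory test.

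The figures assume proportional hazards, 55% control mortality, a log HR variance of 4/deaths, and no re-calculation of deaths or futility stop. The futility thresholds are confidential, so the share of trials stopped that way cannot be computed. The interval in step 3 is approximate and not adjusted for the adaptive design.

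**What to change.** Delete the significance condition under both Outcomes and Primary outcome analyses. State that, whatever the test result and whether or not the trial stops early, the ITT analysis will report:
- 90-day all-cause mortality in each arm, estimated by Kaplan-Meier so that patients censored before day 90 are handled, and the difference between arms, with confidence intervals;
- the hazard ratio that matches the log-rank test, with a confidence interval compatible with the inverse normal group sequential design.

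The cost is a change of wording in two places and a small amount of analysis. An interval adapted to the design is slightly wider than an unadjusted one. The number of deaths, the number of patients and the significance levels stay as they are.
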